Time from initiation of the study intervention to subsequent hospital admission due to an acute wheezing illness within the 12‐month study period. Number of hospital admissions (> 6 h from triage to discharge) due to an acute wheezing illness per child over the 12‐month study period. Illnesses resulting in admission are considered discrete if the patient was without symptoms for at least 72 h between the end of one episode and the beginning of the next. Number of wheeze episodes per child over the 12‐month study period. A wheeze episode is defined as a wheezing illness resulting in repeated administration of an inhaled bronchodilator. Once again, illnesses are considered discrete if the patient was without symptoms for at least 72 h between the end of one episode and the beginning of the next. Total cost of health resource utilisation (hospital, community, pharmaceuticals) per child over the 12‐month study period. Parent or guardian loss of productivity (days of work missed/days out of role) over the 12‐month study period. Cost‐effectiveness of the intervention over the 12‐month study period. Mean duration of wheeze episodes (mean per child are used to calculate the group mean) within the 12‐month study period. Quality of life of the child using the PedsQL [28]; and parents using the EQ5D [30] at the end of the 12‐month study period. Anxiety symptoms in child using the Child Behaviour Checklist (CBCL) [26] at the end of the 12‐month study period.

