### Sample Size

3.9

Prior to trial commencement, the most recently published data suggested an annual readmission rate for preschool wheeze of approximately 20% [31]. ARROW was powered to identify a 25% reduction in this rate, which CIRCAN investigators nominated as the minimum effect size required to change current practice. This required 1814 participants (907 per treatment group) based on a two‐sided chi‐squared test with 80% power and an alpha level of 0.05. Allowing for a 20% loss to follow‐up, we planned to recruit 2268 participants (1134 participants per group). However, as of March 2024, the ARROW participants' observed readmission rate for wheezing illnesses over 12 months was 33%, possibly reflecting the recruitment of children with relatively more severe preschool wheeze. This is consistent with a 2023 cohort study reporting a 12‐month readmission rate among children with asthma aged 3–18 years of 34% [32]. Given this, in 2024, we recalculated the required sample size assuming a 35% readmission rate in the placebo group. Retaining a 25% reduction in the admission rate as the minimum effect size needed to change practice (down to 26.25%), we recalculated the required sample size to be 870 participants (435 per treatment group). Allowing for 20% loss to follow‐up, we aimed to recruit 1088 participants (544 per treatment group).

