### Statistical Methods

3.10

Data collection and reporting will follow the CONSORT guidelines, and analyses will be conducted according to the intention‐to‐treat principle, using a treatment policy strategy for all intercurrent events, as detailed in the statistical analysis plan (SAP). The estimand of interest for the primary outcome (hospital admission for wheeze within 12 months) is the odds ratio for OM‐85 compared with placebo, which will be estimated via logistic regression adjusted for stratification factors (age group, number of admissions, and pharmacy location reflecting the country of enrolment). There are no planned interim analyses. Missing data will be managed as per the study protocol and SAP.

The estimand of interest for the binary secondary outcomes is the (adjusted) odds ratio estimated as for the primary outcome. The estimand of interest for the time to readmission is the hazard ratio for the treatment effect, which will be estimated using a Cox Proportional‐Hazards model, censoring participants with no readmissions at the end of the 12‐month follow‐up, adjusted for the stratification factors. The estimand of interest for the number of readmissions and wheeze episodes is the incidence rate ratio, which will be estimated via Poisson regression adjusted for the stratification factors. The estimand of interest for the secondary outcomes of health resource utilisation, parent/guardian loss of productivity, duration of wheeze episodes and parent and child quality of life will be the difference in means between the treatment groups estimated using linear regression adjusted for the stratification factors. All results will be presented with 95% CIs and corresponding *p* values.

The primary economic analysis will be a cost‐effectiveness analysis from a healthcare perspective, comparing the difference in the primary outcome measure with the difference in costs between groups. Costs include the cost of OM‐85 and direct costs of all health service use, including hospital visits, community health services and pharmaceutical use. The secondary economic analysis will assess the impact of the intervention on families including parent‐reported out‐of‐pocket costs, loss of productivity and quality of life outcomes, through a cost‐consequences analysis from a societal perspective that compares the impact of OM‐85 on all measured outcomes to the difference in all costs (to health system, work, and family).

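### Section 3.10 names Poisson regression alone for the admission and wheeze-episode counts and makes no provision for overdispersion, which is likely in this population

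*Protocol article*

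**What the plan says.** Table 3 (section 3.8, Outcomes) lists two counts among the secondary outcomes. One is hospital admissions "due to an acute wheezing illness per child over the 12‐month study period"; the other is "Number of wheeze episodes per child over the 12‐month study period". Repeat events in the same child are counted separately: "illnesses are considered discrete if the patient was without symptoms for at least 72 h between the end of one episode" and the start of the next.

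Section 3.10 (Statistical Methods) gives both counts the same estimand and model: the "incidence rate ratio, which will be estimated via Poisson regression adjusted for the stratification factors". It then promises inference on every outcome: "All results will be presented with 95% CIs and corresponding" *p* values. It does not say how standard errors for the Poisson model will be obtained. It mentions neither a dispersion parameter nor an alternative count model. The section cites the SAP for the intention-to-treat and intercurrent-event analysis and for missing data; the SAP is not shown.

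The stratification factors (section 3.4) are three binary variables: fewer than two versus two or more wheeze admissions in the past year, age under three versus three or over, and one of two pharmacy locations.

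**The concern.** A Poisson model with its default standard errors assumes that, within strata, the variance of the count equals its mean. That holds only if children in the same stratum share one underlying event rate, which is unlikely here. Entry requires recurrent wheeze, ages run from 1 to under 6 years, more than 40 hospitals in two countries recruit, and routine wheeze treatments continue at the treating team's discretion. Stratifying by prior admissions and age shows that the investigators themselves expect risk to differ between children. Two-level factors leave much of that variation inside the strata.

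If residual variation exists and default standard errors are used, the incidence rate ratio is still estimated sensibly but its precision is overstated. These two counts are the main measures of recurrent burden. A frequency benefit could therefore look statistically secure when it is not, including in a trial whose primary result is null.

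**Working it through.** **The plan's own figure.** The only sample size calculation is for the binary primary outcome (section 3.9), "based on a two‐sided chi‐squared test with 80% power and an alpha level of 0.05". For the revision, "we recalculated the required sample size assuming a 35% readmission rate in the placebo group", against 26.25% on OM-85. With the pooled-variance two-proportion formula, the mean proportion is 0.30625 and n per group = [1.96 × √(2 × 0.30625 × 0.69375) + 0.8416 × √(0.35 × 0.65 + 0.2625 × 0.7375)]² / 0.0875² = 434.4, rounded up to 435. That gives 870 in total, and 435 / 0.8 gives 544 per group (1088) after 20% loss. The stated figures reproduce. No mean, variance or power is stated for either count.

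**Inputs for the counts**
- Admissions: 35% of placebo children with at least one (section 3.9).
- Episodes: the Introduction reports an earlier trial with a reduction of 2.18 episodes, 38% relative. If 38% is relative to the placebo mean, that mean is 2.18 / 0.38 = 5.74 and the treated mean is 5.74 − 2.18 = 3.56.
- Dispersion k: assumed. It is the squared coefficient of variation of children's underlying rates within strata, so k = 0.1 means a between-child SD of √0.1 = 32% of the mean.

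**Formulas (gamma-Poisson counts)**
- Variance / mean: φ = 1 + kμ.
- Mean admissions with P(at least one) held at 35%: μ = (0.65^(−k) − 1) / k, or −ln 0.65 = 0.43 when k = 0.
- Interval width relative to the correct width: 1 / √φ.
- True type I error of the nominal 5% test: 2 × [1 − Φ(1.96 / √φ)].

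Example, admissions at k = 1: μ = 1 / 0.65 − 1 = 0.54; φ = 1.54; width 1 / √1.54 = 81%; type I error 11.4%.

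The last two columns of the table come from simulation: 870 children, no treatment effect, 1,500 runs per row, and a Poisson model adjusted for three binary factors. Monte Carlo SE is about 0.6 points at a true 5%.

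| Count | k | μ | φ | Interval width | Type I, formula | Type I, simulated, model-based SE | Type I, simulated, robust SE |
|---|---|---|---|---|---|---|---|
| Admissions | 0 | 0.43 | 1.00 | 100% | 5.0% | 6.3% | 6.5% |
| Admissions | 0.5 | 0.48 | 1.24 | 90% | 7.8% | 8.3% | 5.7% |
| Admissions | 1 | 0.54 | 1.54 | 81% | 11.4% | 10.8% | 4.9% |
| Admissions | 2 | 0.68 | 2.37 | 65% | 20.3% | 19.4% | 5.3% |
| Episodes | 0 | 5.74 | 1.00 | 100% | 5.0% | 6.0% | 5.9% |
| Episodes | 0.1 | 5.74 | 1.57 | 80% | 11.8% | 12.3% | 4.7% |
| Episodes | 0.3 | 5.74 | 2.72 | 61% | 23.5% | 23.5% | 4.8% |
| Episodes | 0.5 | 5.74 | 3.87 | 51% | 31.9% | 32.3% | 5.1% |

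At the lower mean of 3.56 episodes, k = 0.1 to 0.5 gives 9.2% to 24.0% by the formula. Scaling the standard errors by the Pearson statistic did as well as the robust estimator. Across the two corrections, simulated error lay between 4.7% and 6.5% in every setting.

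**What the documents say about dispersion.** The only variance information is the earlier trial's interval, −3.22 to −1.13, so SE = (3.22 − 1.13) / (2 × 1.96) = 0.533. Setting SE² = φ(5.74 + 3.56) / n gives φ = 1 at about 33 children per arm. The article does not give that trial's size. At an assumed 30, 40, 50 or 60 per arm, φ would be 0.92, 1.22, 1.53 or 1.84. This neither establishes nor excludes overdispersion.

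**The case against.** The strongest objection is that the article names a mean model and an estimand but no variance estimator. Poisson regression with robust standard errors fits the text exactly as written, and a condensed article may leave the variance estimator to the SAP. This stands in part. A reader might infer that the plan commits to model-based standard errors, or that false precision is certain; the documents support neither. What remains is that the article does choose a model. It gives one method for both counts, promises intervals and *p* values from it, and in that section refers to the SAP for other matters. Followed literally, the sentence leads to default Poisson output.

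The evidence for overdispersion is also indirect. A reader might take the roughly 65% of children without an admission as a sign of it, but a pure Poisson count with mean 0.43 gives the same share, since exp(−0.43) = 0.65. The case rests on the design and on clinical plausibility, not on a figure in the documents.

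Finally, a reader might infer from the absence of an exposure term, alongside the 20% allowance for loss, that unobserved weeks will be scored as event-free. The documents do not support that. Section 3.10 refers missing data to the full protocol and SAP, an incidence rate ratio is compatible with a person-time offset, and the 20% is a recruitment allowance rather than a scoring rule.

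**Conclusion.** The point holds conditionally. Poisson regression is the only model named for two recurrent-event counts, with no provision for overdispersion, and overdispersion is likely. If it is present and model-based standard errors are used, type I error is about 8% to 20% for admissions (k 0.5 to 2, 35% with at least one admission) and about 12% to 32% for episodes (mean about 5.7, k 0.1 to 0.5). Intervals are then 90% to 65% and 80% to 51% of their correct width, respectively. These sizes rest on assumed gamma-Poisson counts and assumed k; with k = 0 the error is 5%.

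The primary logistic analysis and the sample size of 870 are unaffected, as is the choice of estimand. This should be fixed, but it does not threaten the trial's main conclusion.

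**What to change.** In section 3.10, and in the SAP if it does not already say so, state that the number of admissions and the number of wheeze episodes will each be analysed by negative binomial regression, or by Poisson regression with robust (sandwich) standard errors, adjusted for the stratification factors. Choose one of the two before unblinding. The incidence rate ratio stays as the estimand. The simulation tested the robust and Pearson-scaled Poisson versions, not the negative binomial, which is the model matching the gamma-Poisson counts assumed here.

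The cost is one sentence. Intervals will be wider where the counts are overdispersed; where they are not, little is lost. If the SAP already specifies such a method, the sponsor need only confirm it and bring the article's sentence into line.

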### Ethics and Dissemination

3.11

Ethics approval was granted by The Royal Children's Hospital Melbourne Human Research Ethics Committee (RCH HREC Reference number: 64007) on 21st September 2021 (Current protocol version 1.7, June 2024) and the Health and Disability Ethics Committee in NZ (Ethics reference: 2022 FULL 11630) on 17th October 2022 (Current protocol version 1.9, May 2024). Approved protocol amendments are communicated to the PI team and to participating sites where relevant. The trial is being conducted in accordance with the ICH Guidelines for Good Clinical Practice [33]. Findings will be published in peer‐reviewed international journals.

### Patient and Public Involvement

3.12

Before and after commencing the trial, a focus group of parents of preschool‐aged children was held in Australia to seek feedback regarding the information video, promotional materials, PICF, recruitment process, trial requirements and maximising participant engagement. Feedback was considered and incorporated into the study design. During and after their participation in the trial, all participants are invited to provide feedback, and trial processes are adapted as necessary. Frequent feedback is sought from clinicians at participating sites to assist in implementing strategies to maximise engagement and referral numbers.

## Discussion

4

ARROW will be the first trial of sufficient size to determine whether treatment with a bacterial lysate reduces the risk of hospital readmission among children with preschool wheeze—a primary outcome prioritised by clinicians, policymakers, and families. The concept and protocol were developed in consultation with members of CIRCAN, informed by consumer priorities. Recruitment strategies in Australia and New Zealand differ, but each is well‐suited to its setting. In Australia, the decentralised design is novel and cost‐effective, providing access to families living in regional and remote settings and minimising the burden on referring hospitals. In New Zealand, recruitment aligns with cultural, social, and family preferences, offering both face‐to‐face and remote engagement options for participants.

The ARROW trial has several important strengths. Extensive end‐user engagement from inception, combined with the large number of participating sites, will accelerate the translation of the study's findings into clinical practice [34]. The primary outcome is robust and clinically important. The recruitment strategy, pragmatic design, and minimised participant burden support the feasibility of a trial with sufficient statistical power. The emphasis on providing access to regional and rurally based families in Australia, and on culturally and socially appropriate methods in New Zealand, supports the diversity of participants and, hence, the generalisability of the findings.

Limitations include the reliance on caregivers for the administration of the study medication and data collection. However, primary outcome data are verified by hospital records. The absence of biological sampling prevents the investigation of mechanistic pathways, noting that these are being investigated in other, smaller OM‐85 clinical trials with a higher participant burden (NCT05857930).

ARROW is an efficient, pragmatic trial addressing a critical knowledge gap. If found to be effective, end‐user engagement from inception and throughout the trial, spanning over 40 centres, will facilitate the rapid translation of the findings into practice and policy, leading to improved health outcomes for children with preschool wheeze in Australasia and internationally.

## Data Availability

Data will be stored at Deakin University, Australia. The study protocol, DSMB charter, statistical analysis plan, and data collection tools may be made available on request.

